## **5. A description of the stopping rules for individuals, parts of trial and entire trial**

with a H5N1 vaccine will be conducted using blood and oral fluid samples at the University of Bergen. The detailed immunological response will be studied using a variety of immunological methods e.g. serum antibody (HI, ELISA for antibody class and IgG subclasses, neuraminidase assays), peripheral blood antibody secreting cells (e.g. ELISPOT and non secreted IgG from B cells), lymphocyte profiles (e.g. FACS analysis) and cytokine producing T-cells (e.g. ELISPOT, ELISA, multiplex analysis). The long lasting and cross reactive immunity will be studied (National Institute of Biological Standards and Control and Health Protection Agency, UK, Istituto Superiore di Sanità, University of Bergen) using established appropriate immunological assays e.g. ELISA, HI, SRH, or FACS analysis of lymphocytes stimulated *in vitro* with different H5 strains. Sera may also be used in other serological tests deemed appropriate for detection of influenza specific responses e.g. western blots, pseudotype assays and epitope mapping using the phage display system.

forms. A daily log will be kept of all events related to the trial. On the day of vaccination, each subject will be randomly allocated a unique subject identification number in order to protect confidentiality. The original source documentation will be a paper-based database, which will include the original hard copy of the results from the two computer databases (referred to below) of the screening samples and serological results, and other information related to clinical trial. All databases will be secured against unauthorised access and confidentiality will be maintained at all times. One paper database will be held at the immunisation clinic at the hospital and will contain personal data (name, sex, age, contact details, next of kin, and the National Personal Identification Number (personal number) and the screening test results. The screening test results will be stored in NetLab database and only the relevant Haukeland University Hospital laboratory staff will have access to this database, by use of his/her personal access code to the hospital database. The second database will be laboratory-based and contain the subject identification number and data relating to immunological responses, the only personal data will be age, sex and previous influenza history. The sponsor or her nominee will only have access to this database and it will be secured against unauthorised access.

## 6 Selection and Withdrawal of subjects

### 1. Subjects inclusion criteria

- The following subjects will be considered eligible to enter the study or receive the second dose of vaccine:
- Healthy volunteers (as concluded from the medical history, physical examination, and clinical judgment) aged 19 to 50 years old
  - Females using a reliable method of contraception (from 4 weeks prior to the first vaccination until 4 weeks after the second vaccination) and a negative urine pregnancy test will be required before administration of each dose of vaccine
  - Signed informed consent
  - Subjects able to understand and comply with the study protocol and complete the Adverse Event Form
  - Subjects able to attend the scheduled visits

- Subjects with normal pre-screening values. If a subjects prescreening samples lie outside the reference values he/she will only be included in the study based upon the medical evaluation of the clinical investigator

## 2. Subjects exclusion criteria

The following subjects will not be considered eligible to enter the study or receive the second dose of vaccine:

- Persons with a history of anaphylaxis or serious reactions to any vaccine
- Persons with known hypersensitivity to any of the vaccine components
- Persons who have had a temperature  $>38^{\circ}\text{C}$  during the previous 72 hours
- Persons who have had an acute respiratory infection during the last 7 days
- Women who are pregnant or breast-feeding
- Persons with chronic illness at any stage that could interfere with trial conduct or compliance
- Persons who have received blood products or immunoglobulins parenterally during the previous 3 months
- Persons who have been vaccinated with any vaccine during the 4 weeks preceding the first trial vaccination
- Persons with known or suspected immunosuppressive disease or who use systemic immunosuppressive drugs
- Persons taking immunostimulant therapy
- Persons involved in another clinical trial during the last month.
- Suspected non-compliance

## 3. Subjects withdrawal criteria

When and how to withdraw subjects from the trial

The clinical investigator will evaluate the local and systemic adverse reactions of each subject. If a subject experiences unexpected serious local or systemic reactions then he/she may be withdrawn from the study. The screening samples should be within the normal range (see Table 6.1). Subjects that have out of range values will be withdrawn from the study, if the responsible clinician believes it to be in their best interest.

The type and timing of data to be collected for withdrawn subjects

The subjects who are withdrawn by the clinical investigator from the trial will continue to receive the clinically necessary screening tests as scheduled in the trial protocol. The clinical investigator will also conduct more frequent tests if deemed clinically necessary. No further trial samples will be collected from subjects who withdraw their informed consent for their participation in the study.

Whether and how subjects are to be replaced

Subjects will not be replaced if they are withdrawn or voluntarily withdraw from the trial

The follow-up for subjects withdrawn from treatment

This study is a vaccine study and subjects who are withdrawn will not receive the second dose of vaccine, if they are withdrawn after the first dose. The subjects who are withdrawn from the trial will continue to receive the screening tests, if clinically necessary, as described in the protocol and if deemed clinical necessary these tests will be carried out more frequently.

## 7. Treatment of Subjects

1. Treatment to be administered including name of all products, the doses, the dosing schedule, the route of administration and the treatment periods including follow-up periods for the subjects for each product treatment group.

Sixty healthy subjects aged 19-50 years who will receive two doses of H5N1 influenza vaccine by intramuscular injection into the deltoid muscle, separated by  $21 \pm 4$  days. Escalating doses will be separated by a period of one week. Four groups of 15 subjects will receive two doses of pandemic virosomal A/H5N1 influenza vaccine containing

|         |                                                                     |
|---------|---------------------------------------------------------------------|
| Group 1 | 30µg HA IM,                                                         |
| Group 2 | 1.5µg HA adjuvanted with 50µg 3 rd generation ISCOM™ IM, |
| Group 3 | 7.5µg HA adjuvanted with 50µg 3 rd generation ISCOM™ IM, |
| Group 4 | 30µg HA adjuvanted with 50µg 3 rd generation ISCOM™ IM.  |

The second vaccine dose will contain the same quantity of antigen and adjuvant as in the first dose. Each subject will be enrolled in the trial for 1 year. They will be involved in the trial for a period of 10 weeks, during which blood samples will be collected at days 0, 3, 7, 14 and 21 days after each dose of vaccine. All subjects will be asked to voluntarily provide trial blood samples at 6 and 12 months after first dose of vaccine to examine the longevity of the antibody response.

Subjects will be pre-screened to ensure that they meet the entry criteria, and screened during the study for haematological, biochemical and immunological parameters to evaluate any systemic adverse events reactions.

The following parameters will be studied

- **Haematology:** red blood cell count, white blood cell count, % of neutrophils, eosinophils, basophils, monocytes, lymphocytes, platelets, haemoglobin haematocrit, mean cell volume
- **Biochemical parameters:** CRP, transaminases (ASAT, ALAT), alkaline phosphatase, Gamma GT, total bilirubin, total protein, albumin, glucose, blood creatinine, blood urea,
- **Immunology tests:** ANA antibodies

## 2. The methods and timing of the screening tests

Subjects will be pre-screened for haematological, biochemical and immunological tests to ensure they meet the inclusion criteria for the study. During the study, haematological, biochemical and immunological tests will be conducted to ensure that the vaccine is well tolerated. Blood samples will be collected at day 3 to examine for acute reactions and at 21 days after 1st and 2nd dose of vaccine to examine for longer term adverse events as detailed in the Table 9.1. The normal values for the screening samples are shown in Table 9.2.

Table 9.1 The timing of the screening tests

| Timing of samples                                                          |                            | Haematology            |                                                                    | Biochemistry               | Immunology     |
|----------------------------------------------------------------------------|----------------------------|------------------------|--------------------------------------------------------------------|----------------------------|----------------|
| Pre-screen, days 0, 3, 21                                                  | red blood cell count       | white blood cell count | (% of neutrophils, eosinophils, basophils, monocytes, lymphocytes) | CRP                        |                |
|                                                                            | after each dose of vaccine |                        |                                                                    |                            |                |
| Pre-screen, 21 days after 1 st and 2 nd vaccine dose | platelet count             | haemoglobin            | haematocrit                                                        | transaminases (ASAT, ALAT) | ANA antibodies |
|                                                                            | mean cell volume           |                        |                                                                    |                            |                |
| Pre-screen, 21 days after 2 nd vaccine dose                     | total bilirubin            | gamma GT               | phosphatase                                                        | alkaline                   | total protein  |
|                                                                            |                            |                        |                                                                    |                            |                |
|                                                                            | albumin                    | glucose                | blood creatinine                                                   | blood urea                 | LD             |

Table 9.2 Normal reference ranges for the screening tests.

| Haematological parameters |                              | Biochemical parameters |                | Immunology tests |               |
|---------------------------|------------------------------|------------------------|----------------|------------------|---------------|
| red blood cell count      | 3.7-5.8 10  /L  | CRP                    | <10 mg/L       | ANA antibodies   | <0.99 (ratio) |
| white blood cell count    | 3.5-11.0 10  /L  | ASAT                   | 15-45 U/L      |                  |               |
| neutrophils               | 1.7-8.2 10  /L   | ALAT                   | 10-70 U/L      |                  |               |
| eosinophils               | 0.0-0.7 10  /L   | alkaline phosphatase   | 35-105 U/L     |                  |               |
| basophils                 | 0.0-0.3 10  /L   | Gamma GT               | 15-115 U/L     |                  |               |
| monocytes                 | 0.04-1.30 10  /L | total bilirubin        | 5-25 µmol/L    |                  |               |
| lymphocytes               | 0.7-5.3 10  /L   | albumin                | 36-45 g/L      |                  |               |
| platelets                 | 145-348 10  /L   | glucose                | 4.0-6.0 mmol/L |                  |               |
| haemoglobin (female)      | 11.6-16.0 g/dL               | blood creatinine       | 60-105 µmol/L  |                  |               |
| haemoglobin (male)        | 13.2-16.6 g/dL               | blood urea             | 2.6-8.1 mmol/L |                  |               |
| haematocrit               | 0.40-0.50 l                  |                        |                |                  |               |
| mean cell volume (MCV)    | 80-102 fL                    |                        |                |                  |               |

1. **Specification of efficacy parameters**

In the absence of true efficacy markers like prevention of illness and/or reduction of morbidity and mortality, serum anti-HA antibodies are the most commonly measured correlate of protection against influenza [57] or surrogates of efficacy. The CHMP have defined criteria for the annual update for seasonal influenza vaccines, which measure the serological responses by the haemagglutination inhibition or single radial haemolysis assays. An HI titre  $\geq 40$  (or an equivalent SRH  $> 25\text{mm}^2$ ) indicates 50% protective levels of serum antibody against influenza infection in man. The EU evaluation criteria in groups of at least 50 adults aged 18-60 approximately at 3 weeks after vaccination are:

  - The number of seroconversions or significant increases in anti-haemagglutinin antibody titre should be  $> 40\%$ ;
  - Mean geometric increase  $> 2.5$ ;

## 8 Assessment of Efficacy

4. **Procedures for monitoring subject compliance**

This study is a vaccine study and the daily log of events and CRF will be used to record if subjects have been vaccinated and provided the appropriate trial samples.

3. **Medication permitted (including rescue medication) and not permitted before and /or during trial**

All subjects enrolled in this trial may continue their normal medication throughout the study. Subjects may continue to take therapy for chronic medical conditions, but must be maintained on a stable regimen for at least 2 weeks prior to study entry as assessed by their Medical History. However, subjects taking medication for malignant diseases or medication which may cause immunosuppression, will be excluded from enrolling in this study.

If anaphylactic shock occurs after vaccination, it will be treated according to the standard routines at Haukeland University Hospital using hydrocortisone sodium succinate (Solu-Cortef 100mg), dexchlorfeniramine (5mg/mL), atropine (1mg/mL), adrenaline (1mg/mL and 0.1mg/mL). Use of other medication including over-the-counter products will be discouraged during the study. Investigational drugs are prohibited during the course of the study.

- The proportion of subjects achieving an HI titre  $\geq 40$  or SRH  $> 25\text{mm}^2$  should be  $> 70\%$

The CHMP require for marketing authorisation of a pandemic vaccine that the vaccine fulfils all current evaluation criteria despite the immunological naivety of the host. The serological responses of the four vaccine groups will be evaluated and the ability of each group to meet the CHMP criteria will be determined. The ability of the different vaccine strengths to elicit neutralising antibodies will also be investigated.

In a pandemic situation, it is important to know how rapidly the immune response is elicited after vaccination with a novel subtype [52]. Thus, the detailed kinetics of the immune response in immunologically naive individuals will also be assessed through the induction of local and systemic antibody and cellular immune responses and results will be compared to published results on the response to current influenza vaccines in healthy adults. Furthermore, there is a clear need for improved understanding of the immune response elicited in human volunteers including the quality and repertoire of the antibody response which will be evaluated by ELISA and phage display, respectively. Two other important factors are the capacity of the vaccine to elicit long lasting immunity and cross reactive immunity to H5 influenza viruses [52]. These will be evaluated by the standard serological assays and through the induction of local antibody and systemic cellular immune responses.

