#### European Union (EU) requirements for influenza vaccines

The Committee for Medicinal Products for Human Use (CHMP) has defined a set of regulatory criteria influenza vaccines need to meet in order to obtain a marketing license in the European Economic Area [30]. The vaccine efficacy is tested by the haemagglutination inhibition (HI) [31], or single radial haemolysis (SRH) assays [32]. An HI titre  $\geq 40$  (or an equivalent SRH  $> 25\text{mm}^2$ ) indicates 50% protective levels of serum antibody against influenza infection in man. The EU requirements for harmonisation of influenza vaccines require annual clinical trials for licensing. The vaccine should fulfil one of the following evaluation criteria for each strain in adults aged 18-60:

1. The number of seroconversions or significant increases in anti-haemagglutinin antibody titre should be  $> 40\%$ ;

2. Mean geometric increase >2.5;

3. The proportion of subjects achieving an HI titre  $\geq 40$  or SRH > 25mm^2 should be >70%.

There are no requirements for inactivated vaccines to evoke a cellular immune response. The World Health Organisation (WHO) has prepared a number of recommendations for increased preparedness and research [33]. The CHMP require pandemic vaccine to meet all the current evaluation criteria for marketing authorisation. They also recommend measuring neutralising antibodies, and suggest more detailed analysis of the immune response for example detection of antibodies directed against neuraminidase and cell mediated responses [34].

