## 5 TRIAL DESIGN

- Investigate the long lasting immunity induced by the vaccine
- Examine the ability of the vaccine to induce cross-reactive immunity to H5 strains of different clades
- Evaluate the quality of the immune response induced by the vaccine.

1. A specific statement of the primary endpoints and secondary endpoints to be measured by the trial

The primary endpoints of the trial are the local and systemic adverse events and tolerability of parenterally administered virosomal H5N1 influenza vaccine with or without 3rd generation ISCOMTM adjuvant. The secondary endpoints are the evaluation of the immunogenicity of a non-adjuvanted and 3rd generation ISCOMTM adjuvanted virosomal H5N1 influenza vaccine and the ability of the vaccine to meet the CHMP evaluation criteria.

The immunogenicity of the H5N1 vaccine will be assessed through the induction of specific local and systemic antibody and cellular immune responses, and analyses of the epitopes to which the response is directed. Furthermore the capacity of the vaccine to elicit cross reactive and long lasting immunity will be evaluated. In a pandemic situation, an important aspect is the rapidity of the immune response to the H5N1 vaccine and therefore the detailed kinetics of the immune response will be investigated.

A description of the type/design of trial to be conducted

The clinical trial will be an open phase I dose escalating pilot study in 60 healthy subjects aged 19-50 years who will receive two doses of vaccine, separated by 21 ± 4 days, by intramuscular injection into the deltoid muscle. Escalating doses will be separated by a period of one week. Four groups of 15 subjects will receive two doses of pandemic virosomal A/H5N1 influenza vaccine containing

|         |                                                                                  |
|---------|----------------------------------------------------------------------------------|
| Group 1 | 30µg HA IM,                                                                      |
| Group 2 | 1.5µg HA adjuvanted with 50µg 3 rd generation ISCOM TM IM, |
| Group 3 | 7.5µg HA adjuvanted with 50µg 3 rd generation ISCOM TM IM, |
| Group 4 | 30µg HA adjuvanted with 50µg 3 rd generation ISCOM TM IM.  |

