## 2. Methods and timing for assessing recording and analyzing efficacy parameters

Blood samples will be taken for serological assays at days 0, 3, 7, 14 and 21 after 1st and 2nd doses of vaccine. This study is an open study but all sera will be coded and blinded assays will be conducted by National Institute of Biological Standards and Control, Health Protection Agency and Istituto Superiore di Sanità, (SRH, HI, and neutralisation assays) on samples collected up to 21  $\pm$  4 days after second dose of vaccine. These assays will be run with the international human anti-H5N1 standard plasma pool to allow comparison with other H5N1 pandemic clinical trials. When these serological assays are completed the code will be broken and the results sorted into appropriate vaccine group. The influence of the use of adjuvant and different antigen strengths on the immunogenicity of a viral A/H5N1 influenza vaccine on each of the sampling days and particularly 21 days post vaccination will then be assessed according to the three evaluation criteria defined by the CHMP. For each vaccine group the following will be calculated:

- The number of subjects who seroconvert or show significant increases in anti-haemagglutinin antibody titre;

- The mean geometric increase;

- The proportion of subjects achieving an HI titre  $\geq 40$  or SRH  $> 25 \text{ mm}^2$ .

The immunogenicity of the vaccine will also be evaluated by

- Producing a detailed time course of the immune response to vaccination including the kinetics of the T, B- and serum antibody responses
- The ability of the vaccine to induce long lasting immunity using the blood samples collected at 6 and 12 months after vaccination.
- The ability of the vaccine to induce cross-reactive immunity to other H5 strains.
- Examining the quality and repertoire of the antibody response.

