**2. The number of subjects planned to be enrolled and reason for choice of sample size**

Sixty young healthy subjects (aged 19-50 years old) will be randomly assigned to one of four groups, each group will contain 15 subjects and the investigators will aim to have an equal distribution of males and females in each group and similar age distribution.

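### CHMP criteria stated for groups of at least 50 are applied to groups of 15 and also serve as the yardstick for adjuvant and antigen-dose effects; at 15 the grey zone around each threshold is much wider

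*Protocol*

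**What the plan says.** The protocol makes the CHMP criteria part of a secondary endpoint: section 5.1 lists "the ability of the vaccine to meet the CHMP evaluation criteria" beside immunogenicity. Section 8.1 introduces the criteria with "The EU evaluation criteria in groups of at least 50 adults aged 18-60 approximately at 3 weeks after vaccination are", and gives three: seroconversion or significant increase above 40%, a geometric mean increase above 2.5, and a proportion above 70% with HI titre of at least 40 or SRH above 25 mm². It notes that a pandemic vaccine has to meet all three. It then states that "the ability of each group to meet the CHMP criteria will be determined". On group size, section 10.2 says that "each group will contain 15 subjects", and section 6.3 does not replace withdrawals.

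Section 8.2 turns to the effect of adjuvant and antigen strength, on each sampling day and especially 21 days after vaccination. It says that this influence "will then be assessed according to the three evaluation criteria defined by the CHMP". It then lists what is calculated for each vaccine group: the number who seroconvert or show a significant rise, the geometric mean increase, and the proportion reaching the HI or SRH level. It names no between-group contrast.

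Section 10.1 says that the trial is a phase I study in a limited number of subjects and that a larger study with more power would be needed. No passage reconciles 15 with 50 or calls the CHMP results descriptive.

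**The concern.** Two things are at issue. First, the protocol quotes a criterion together with the group size it belongs to and then applies it to groups less than a third of that size, without comment. Second, the same criteria are the stated basis for judging adjuvant and dose. A result per group is not a comparison between groups: one formulation at 11/15 and another at 10/15 fall on opposite sides of the 70% line, yet differ by one subject.

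Dose sparing is an explicit aim (section 4), and fulfilment of the CHMP criteria is on the list of planned publications (section 16, running on into section 17). If groups are sorted by which criteria they meet, chance differences could steer the choice of formulation for the next study.

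**Working it through.** **Inputs from the protocol.** Group size 15 (sections 5 and 10.2). Group size attached to the criteria: at least 50 (section 8.1). Thresholds: above 40%, above 2.5, above 70%. The protocol gives no expected rates, SD of log titre, alpha or power, so the 15 cannot be reproduced from inputs; only 4 × 15 = 60 can be checked.

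**Counts needed.** The thresholds are strict.
- 70% criterion: 10/15 = 66.7% misses and 11/15 = 73.3% meets. At 50, 35/50 = 70% misses and 36/50 meets.
- 40% criterion: 6/15 = 40% misses and 7/15 = 46.7% meets. At 50, 20/50 = 40% misses and 21/50 meets.

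**Probability of meeting the criterion.** P(X ≥ k) with X binomial(n, p):

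| Criterion | True rate p | n = 15 | n = 50 |
|---|---|---|---|
| above 70% | 50% | 0.06 | 0.001 |
| above 70% | 60% | 0.22 | 0.05 |
| above 70% | 70% | 0.52 | 0.45 |
| above 70% | 80% | 0.84 | 0.94 |
| above 70% | 90% | 0.99 | 1.00 |
| above 40% | 30% | 0.13 | 0.05 |
| above 40% | 40% | 0.39 | 0.44 |
| above 40% | 50% | 0.70 | 0.90 |

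So a true 80% misses the 70% criterion with probability 1 − 0.836 = 0.16 at 15, against 1 − 0.939 = 0.06 at 50.

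**Precision of a group that just passes.** Exact (Clopper-Pearson) 95% intervals: 11/15, 45% to 92% (36/50, 58% to 84%); 7/15, 21% to 73% (21/50, 28% to 57%). At 15 per group the lower limit exceeds 70% only at 15/15; at 14/15 it is 68%. It exceeds 40% only from 11/15.

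**Geometric mean increase.** The interval is the observed value multiplied and divided by 10^(t × SD/√15), with t = 2.145 on 14 degrees of freedom. The SD is not in the protocol, so a range is assumed. Around an observed 2.5 the 95% interval is 1.7 to 3.7 if the SD is 0.3 log10, and 1.0 to 6.1 if it is 0.7.

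**Two groups with the same true rate.** They get opposite results with probability 2q(1 − q), where q is the probability of meeting the criterion. On the 70% criterion:
- true 60%: 2 × 0.217 × 0.783 = 0.34 at 15, against 0.10 at 50
- true 80%: 2 × 0.836 × 0.164 = 0.27 at 15, against 0.11 at 50
- true 70%, on the threshold itself: 0.50 at 15, against 0.49 at 50

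The last line shows nothing about group size. The first two do.

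**What a direct contrast offers.** Two-sample t-test on log10 titre, 15 against 15, two-sided 5%, assumed SD 0.6 log10: power 26% for a 2-fold, 56% for a 3-fold and 76% for a 4-fold difference. These figures depend on the assumed SD. The reason to prefer the contrast is that it addresses the question asked, not that it guarantees adequate power.

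**The case against.** The strongest reply is that this is an open phase I pilot with safety as its primary endpoint, that section 10.1 admits the limit of size, and that intervals and model-based contrasts are ordinary content of an analysis plan not shown here. That lowers the stakes. It does not remove the mismatch: section 10.1 asks for a larger study but does not qualify the per-group determination. An analysis plan could add intervals, but it would inherit an endpoint worded as meeting the criteria and a comparison tied to them.

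Several stronger readings are tempting, and the documents do not support them.

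- *Verdicts at 15 are a coin toss.* On the threshold this is true at any size: 0.52 at 15 and 0.45 at 50. Four groups all at a true 70% fail to agree 87% of the time at either size. Only the wider grey zone is due to the 15.
- *The endpoint cannot be determined at all.* Too absolute. At a true 90% the 70% criterion is met 99% of the time, and at a true 50% only 6%.
- *Adjuvant and dose effects are read solely from pass/fail verdicts.* Section 8.2 lists counts, a geometric mean increase and proportions, and repeats no cut-offs there. The section on deviations refers to comparative serological analyses. What is missing is a stated between-group contrast.
- *Accepting either HI or SRH inflates the pass rate.* Sections 2.7 and 8.1 present SRH as an equivalent alternative to HI, which most naturally does not mean counting a subject positive on either. The protocol does leave open which assay decides.
- *Many sampling days give many chances to pass.* Section 8.2 singles out 21 days after vaccination and section 8.1 about three weeks, though neither says after which dose. Requiring all three criteria also works against false passes.

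**Conclusion.** The concern holds in limited form. The protocol attaches the criteria to groups of at least 50, applies them to groups of 15 without qualification, and makes them the yardstick for adjuvant and antigen dose using per-group results only. For true rates 10 percentage points from a threshold, the wrong verdict is about three times as likely as at 50: 0.22 against 0.05 and 0.16 against 0.06 on the 70% criterion, 0.13 against 0.05 on the 40% criterion when the true rate is 30%. Differing verdicts between groups are therefore weak evidence of an adjuvant or dose effect unless the rates lie far from the thresholds.

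The binomial figures rest only on the protocol's sizes and thresholds and the true rates shown. They take each criterion alone and assume 15 evaluable subjects. The intervals for the geometric mean increase and the power figures rest on assumed SDs. Because this is a secondary endpoint of a pilot, the point should be corrected but does not threaten the trial.

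**What to change.** 1. In sections 5.1, 8.1 and 8.2, state that the CHMP results are descriptive because the groups are smaller than the 50 to which the criteria refer.
2. Report each proportion with an exact 95% CI, and the geometric mean increase with a 95% CI, beside the CHMP values.
3. Name the assay that gives the main result and the main time point, including after which dose the 21 days are counted.
4. In section 8.2, base statements on the adjuvant (Group 4 against Group 1) and on antigen dose (Groups 2 to 4) on between-group estimates of log titre with CIs, not on which groups meet or miss the criteria.

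This needs no extra subjects, visits or assays. The cost is that the CHMP statement becomes less favourable, and that the between-group intervals may be wide: with an SD of 0.6 log10, a 2-fold difference would be detected only about a quarter of the time.
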